**Table C. Grading Physical Examination Findings**

|                                     | Grade 1
MILD                                                                                                                                                   | Grade 2
MODERATE                                                                                                                                                                                         | Grade 3
SEVERE                                                                                                                                                                                                                     | Grade 4
LIFE-
THREATENING                                                                                                             |
|-------------------------------------|---------------------------------------------------------------------------------------------------------------------------------------------------------------------------|---------------------------------------------------------------------------------------------------------------------------------------------------------------------------------------------------------------------|-----------------------------------------------------------------------------------------------------------------------------------------------------------------------------------------------------------------------------------------------|------------------------------------------------------------------------------------------------------------------------------------------------------|
| Temperature
* (axillary) | 37.5-37.9°C                                                                                                                                                               | 38.0-39.5°C                                                                                                                                                                                                         | > 39.5°C                                                                                                                                                                                                                                      | Sustained fever, equal or greater than 40.0°C for longer than 5 days                                                                                 |
| Dehydration                  | Less than 2 of the following:
Restless, irritable
Sunken eyes
Drinks eagerly, thirsty
Skin pinch goes back slowly                                             | 2 of the following:
Restless, irritable
Sunken eyes
Drinks eagerly, thirsty
Skin pinch goes back slowly                                                                                                 | Two of the following:
Lethargic or unconscious
Sunken eyes
Not able to drink or drinking poorly
Skin pinch goes back very poorly                                                                                                  | Two of the following + shock:
Lethargic or unconscious
Sunken eyes
Not able to drink or drinking poorly
Skin pinch goes back very poorly |
| Jaundice                     | Slight yellowing of sclera and conjunctiva                                                                                                                                | Moderate yellowing of sclera and conjunctiva, yellowing of mucous membranes                                                                                                                                         | Severe yellowing of sclera and conjunctiva, yellowing of skin                                                                                                                                                                                 | N/A                                                                                                                                                  |
| Chest                        | Mildly increased RR (for age, temperature), transient or localised adventitious sounds                                                                                    | Moderately increased RR, diffuse or persistent adventitious sounds                                                                                                                                                  | Rapid RR (< 2 months > 60, 2-12 months > 50, 1-5 years > 40, adults > 30)* nasal flaring, retractions                                                                                                                                         | Cyanosis                                                                                                                                             |
| Abdomen                      | Normal bowel sounds, mild localised tenderness, and/or liver palpable 2-4 cm below the right costal margin (RCM), and/or spleen palpable, and/or umbilical hernia present | Normal or mildly abnormal bowel sounds, moderate or diffuse tenderness; and/or mild to moderately enlarged liver (4-6 cm below the RCM) and/or spleen palpable up to half-way between umbilicus and symphysis pubis | Severely abnormal bowel sounds, severe tenderness to palpation. Evidence of peritoneal irritation and/or significant enlargement of liver (> 6 cm below the RCM) and/or spleen palpable beyond half-way between umbilicus and symphysis pubis | Absent bowel sounds. Involuntary rigidity                                                                                                            |
| Skin†                        | Localised rash, erythema, or pruritis                                                                                                                                     | Diffuse, maculopapular rash, dry desquamation                                                                                                                                                                       | Vesiculation, moist desquamation, or ulceration                                                                                                                                                                                               | Exfoliative dermatitis, mucous membrane involvement or erythema multiforme or suspected Stevens-Johnson or necrosis requiring surgery                |

|                                                           | Grade 1
MILD                                   | Grade 2
MODERATE                                                                 | Grade 3
SEVERE                                                                  | Grade 4
LIFE-
THREATENING                               |
|-----------------------------------------------------------|-----------------------------------------------------------|---------------------------------------------------------------------------------------------|--------------------------------------------------------------------------------------------|------------------------------------------------------------------------|
| Hearing                                            | < 4 years: N/A
≥ 4 years: Decreased hearing in one ear | < 4 years: N/A
≥ 4 years: Decreased hearing in both ears or severe impairment in one ear | < 4 years: Any evidence of hearing impairment
≥ 4 years: Severe impairment in both ears | N/A                                                                    |
| Tablet test                                        | Difficulty grasping tablet but able to pick up            | Unable to pick up tablet without dropping                                                   | Unable to grasp tablet                                                                     | N/A                                                                    |
| Clinical symptoms / sign (not otherwise specified) | No treatment required; monitor condition                  | Treatment required                                                                          | Requires treatment and possible hospitalisation                                            | Requires active medical intervention, hospitalisation, or hospice care |

Reference – The Harriet Lane Handbook, 15th edition, 2000

† Reference – WHO Toxicity Grading Scale for Determining the Severity of Adverse Events

**TABLE D. Guidelines for Grading of Laboratory Abnormalities**

|                           | Grade 1
MILD | Grade 2
MODERATE | Grade 3
SEVERE | Grade 4
LIFE-
THREATENING |
|---------------------------|-------------------------|-----------------------------|---------------------------|------------------------------------------|
| Haemoglobin (g/dL) | 9.0 – 9.9               | 7.0 – 8.9                   | 5.0 – 6.9                 | < 5.0                                    |

Reference – The Harriet Lane Handbook, 15th edition, 2000†

Reference – WHO Toxicity Grading Scale for Determining the Severity of Adverse Events

## APPENDIX II\*

**Table A. Dihydroartemisinin-piperaquine (DHAPQ)**

DHAPQ tablets are green film coated intended for oral use and contain 20/160mg or 40/320mg of dihydroartemisinin (DHA) and piperaquine phosphate (PQ) respectively.

DHAPQ 20/160 mg Tablets Components

Composition

One tablet contains

| Component                       | Amount
(mg) |
|---------------------------------|----------------|
| Piperaquine Phosphate (ST 3073) | 160            |
| Dehydroartemisinin (ST 3074)    | 20             |
| Starch Maize                    | 34.5           |
| Dextrin                         | 26.4           |
| Hydroxypropylmethylcellulose    | 2.4            |
| Sodium carboxymethylcellulose   | 11.8           |
| Magnesium Stereate              | 2.4            |
| OY-31074 Opadry Green coating   | 7.5            |

The composition of OY-31074 Opadry coating preparation is

| Component                         | (%w/w) |
|-----------------------------------|--------|
| Hydroxypropylmethylcellulose      | 62.501 |
| Titanium Dioxide                  | 25.450 |
| Macrogol 400                      | 6.249  |
| FD&Blue #1 Brilliant blue A1 lake | 0.400  |
| FD&Blue #2 Indigo Carmine A1 lake | 0.400  |
| FD&C Yellow #5 Tartrazine A1 lake | 5.000  |

## DHAPQ 40/320 mg Tablets Components

### Composition

One tablet contains

| Component                       | Amount
(mg) |
|---------------------------------|----------------|
| Piperaquine Phosphate (ST 3073) | 320            |
| Dehydroartemisinin (ST 3074)    | 40             |
| Starch Maize                    | 69             |
| Dextrin                         | 52.8           |
| Hydroxypropylmethylcellulose    | 4.8            |
| Sodium carboxymethylcellulose   | 23.6           |
| Magnesium Stereate              | 4.8            |
| OY-31074 Opadry Green coating   | 15             |

The composition of OY-31074 Opadry coating preparation is the same as above.

Dihydroartemisinin will be given daily. The number of tablets per day is reported in brackets. One tablet of DHAPQ (pediatric tablets) contains 20/40 mg of DHA and 160/320 mg of PPQ.

| Weight in kg | mg of DHA to be given daily | Dose of DHA as mg/kg/d |
|--------------|-----------------------------|------------------------|
| 5 - 6        | 10 (1/2 tablet with 20 mg)  | 1.67 - 2.5             |
| 7 - 12       | 20 (1 tablet with 20 mg)    | 1.67 - 2.86            |
| 13 - 23      | 40 (1 tablet with 40 mg)    | 1.74 - 3.08            |
| 24 - 35      | 80 (2 tablets with 40 mg)   | 2.29 - 3.33            |

*One tablet of DHAPQ contains 40 mg of DHA and 320 mg of PPQ for adult patients.*

Piperaquine will be given daily. The number of tablets per day is reported in brackets. One tablet of DHAPQ (pediatric tablets) contains 20/40 mg of DHA and 160/320 mg of PPQ.

| Weight in kg | mg of PPQ to be given daily | Dose of PPQ as mg/kg/d |
|--------------|-----------------------------|------------------------|
| 5 - 6        | 80 (1/2 tablet with 160 mg) | 13.36 - 20             |
| 7 - 12       | 160 (1 tablet with 160 mg)  | 13.36 - 22.88          |
| 13 - 23      | 320 (1 tablet with 320 mg)  | 13.92 - 24.64          |
| 24 - 35      | 640 (2 tablets with 320 mg) | 18.32 - 26.4           |

*One tablet of DHAPQ contains 40 mg of DHA and 320 mg of PPQ for adult patients.*

**Table B:** Coartem® dose based on body weight will be given daily. Tablets containing 20 mg of Artemether and 120 mg of Lumefantrine.

| Weight in kg  | Number of tablet per dose |
|---------------|---------------------------|
| 5 to < 15 kg  | 1 tablet per dose         |
| 15 to < 25 kg | 2 tablets per dose        |
| 25 to < 35 kg | 3 tablets per dose        |

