### **Artemether –lumefantrine (AL)**

This is a fixed-dose combination of artemether (a semi-synthetic artemisinin derivative) and lumefantrine (a slowly eliminated drug also referred to as benflumetol). The registered indications and branding for AL cover treatment of uncomplicated malaria caused by mono or mixed *Plasmodium* infections. The combination is expected to confer mutual protection against resistance and prevent recrudescence after artemether therapy. The components of this combination were originally studied and developed in China by the Academy of Military Medical Sciences (AMMS), Beijing and Kunming Pharmaceutical Factory (KPF), Kunming. The fixed combination has been registered in China since 1992 and has undergone further development when Novartis signed a collaborative agreement in 1994 with AMMS, KPF and CITITEC, the technology arm of the China International Trust and Investment Corporation (CITIC). Studies for the international registration started in 1995. AL was registered in Switzerland in 1999 and has since received marketing authorisation in several endemic and non-endemic countries. Recently, an agreement was reached between Novartis and WHO for AL to be made available to the public sector of developing countries at a preferential price. Few clinical trials, mostly with the four-dose regimen, have been conducted both with the

original Chinese combination product and the subsequent product used for international registration. A Cochrane review has, in 2003, identified eight randomized, controlled trials comparing AL with standard treatment for uncomplicated falciparum malaria (2117 participants). From the meta-analysis, it was concluded that the four-dose AL regimen was superior to CQ and equivalent to SP in areas of CQ resistance but inferior to mefloquine and mefloquine-artesunate in areas of multidrug resistance. The six-dose regimen was also equivalent to mefloquine-artesunate but was better tolerated. A collaborative project between Novartis and WHO has led to a more user-friendly packaging of the six-dose treatment, which is now being field tested. A paediatric formulation is also being developed and trials have been conducted for regulatory submission to extend the label to cover children who weigh less than 10 kg.

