### ***3.12 Treatment administration***

The study treatment will be administered by health workers under the direct supervision of a licensed physician. The correct number of tablets will be determined using the weight dosing chart. If necessary the study drugs (either whole or as fractions) will be crushed, dissolved in water and squirted into the mouth using a syringe without needle. Administration of all treatments, including AL will be directly observed. After drug administration, patients will be kept for one hour in the clinic. A dose will be repeated in full if vomiting occurs within 30 minutes of administration and halved if vomiting is between 30 minutes and 1 hour post dosing. This event will be documented in the case record form (CRF). If vomiting persists, the patient will be withdrawn from the study and treatment changed (e.g. quinine).

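### Appendix II, which sets tablet numbers, gives no count of artemether-lumefantrine (AL) doses, and its dihydroartemisinin-piperaquine (DHAPQ) table does not fully agree with its own figures

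*Protocol*

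**What the plan says.** Section 3.12 makes the chart the dosing rule: "The correct number of tablets will be determined using the weight dosing chart". The charts are in Appendix II.

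**DHAPQ (Table A).** There are four weight bands: 5-6, 7-12, 13-23 and 24-35 kg. Each has a daily amount, a tablet count and a mg/kg range, shown once for dihydroartemisinin (DHA) and once for piperaquine (PPQ). The lowest band is "10 (1/2 tablet with 20 mg") for DHA, with a stated range of 1.67-2.5 mg/kg, and "80 (1/2 tablet with 160 mg") for PPQ, with a stated range of 13.36-20 mg/kg. The next bands are "20 (1 tablet with 20 mg"), "40 (1 tablet with 40 mg") and "80 (2 tablets with 40 mg").

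**AL (Table B).** The "dose based on body weight will be given daily", with one, two or three tablets for each dose according to weight. The number of doses per day and the total are not given. Section 3.8 and the follow-up charts place treatment on days 0, 1 and 2 in every arm. Section 1.1 discusses a four-dose regimen and a six-dose regimen, including "more user-friendly packaging of the six-dose treatment". It names neither as the regimen of this trial.

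**The other two charts.** The amodiaquine-artesunate (AQ+AS) chart states both frequency and duration. It and the chlorproguanil-dapsone-artesunate (CDA) chart count tablets per day.

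**The concern.** A dosing chart has to lead every site to the same tablets at every eligible weight, and its mg/kg column should follow from its own amounts and weights. Three features of Appendix II fall short of this:

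1. Table B gives tablets for a dose and says the dose is daily, but it does not say how many doses a child receives.
2. One DHAPQ row states mg/kg maxima that its own amounts and weights cannot produce.
3. The DHAPQ bands have whole-kilogram ends with nothing between them, and no rule covers a weight that falls between two bands.

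What is at stake is patient safety and uniform exposure. DHAPQ is given at all 10 sites (1700 children planned) and AL at 8 (8 x 170 = 1360), and DHAPQ against AL is the largest direct comparison. The protocol's own background reports different results for four and six AL doses: in multidrug-resistant areas the four-dose regimen was inferior to mefloquine-artesunate, and the six-dose regimen was equivalent to it. By the protocol's own account, then, the dose count bears on efficacy.

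**Working it through.** **Step 1. Recompute the DHAPQ table.** The inputs are the daily mg amounts and band ends in Table A. The formula is daily mg divided by body weight: the upper band end gives the minimum and the lower band end the maximum.

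| Band (kg) | DHA (mg) | Stated mg/kg | Computed | PPQ (mg) | Stated mg/kg | Computed |
|---|---|---|---|---|---|---|
| 5-6 | 10 | 1.67-2.5 | 1.67-2.00 | 80 | 13.36-20 | 13.33-16.0 |
| 7-12 | 20 | 1.67-2.86 | 1.67-2.86 | 160 | 13.36-22.88 | 13.33-22.86 |
| 13-23 | 40 | 1.74-3.08 | 1.74-3.08 | 320 | 13.92-24.64 | 13.91-24.62 |
| 24-35 | 80 | 2.29-3.33 | 2.29-3.33 | 640 | 18.32-26.4 | 18.29-26.67 |

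The three upper DHA rows reproduce exactly, so the method is the chart's own. The 5-6 kg row does not reproduce:

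- DHA: 10/5 = 2.0 against 2.5 stated; 2.5/2.0 = 1.25.
- PPQ: 80/5 = 16 against 20 stated; 20/16 = 1.25.
- Weight implied by the stated maxima: 10/2.5 = 4 kg and 80/20 = 4 kg. This is below the 5 kg entry weight in section 3.9.

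The two errors are probably one. Apart from one entry, the stated PPQ figures equal 8 times the rounded DHA figures (for example 8 x 1.67 = 13.36, and 8 x 2.5 = 20). That entry is the 24-35 kg maximum: 8 x 3.33 = 26.64 and the direct figure is 640/24 = 26.67, but the table states 26.4. This is a minor miss.

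**Step 2. Weights between bands.** No rounding rule is given. Assume that weight is recorded more finely than 1 kg. Dividing each neighbouring row's DHA amount by the weight gives:

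| Weight (kg) | Lower row | Upper row |
|---|---|---|
| 6.5 | 10/6.5 = 1.54 | 20/6.5 = 3.08 |
| 12.5 | 20/12.5 = 1.60 | 40/12.5 = 3.20 |
| 23.5 | 40/23.5 = 1.70 | 80/23.5 = 3.40 |

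Each pair differs twofold, and each value lies outside the stated range of the row it comes from. The other charts support the assumption: AL and CDA use contiguous bands that run up to, but exclude, the next limit, and the AQ+AS limits are given to 0.1 kg.

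**Step 3. AL dose count.** Set side by side:

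- Table B: a daily dose, in tablets for each dose, with no count.
- Follow-up charts and section 3.8: treatment on three days.
- Section 1.1: four-dose and six-dose regimens only.

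One dose on each of three days makes three doses. In the lightest AL band (one tablet for each dose) the course would be 3 tablets under that reading, against 4 or 6 tablets under the regimens in the background.

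**Step 4. What is not affected.** For AQ+AS, the amodiaquine dose computed over 5 to 35.9 kg is 7.52-15.0 mg/kg, within the stated 7.5-15. The CDA bands are contiguous. DHAPQ tablet counts are unambiguous at whole-kilogram weights.

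**The case against.** **The 5-6 kg error changes no child's tablets.** Section 3.12 makes the tablet count the rule, and both halves of Table A agree on half of the smaller tablet. The mg/kg column only describes it. Few children are likely to be in that band, since six of the ten sites enrol only from 12 months and severe malnutrition is excluded. This stands. A reader might infer that the error touches all 1700 DHAPQ children. It concerns the stated exposure in one row.

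**The gaps may not exist.** The ranges that reproduce use whole-kilogram ends, so the table is complete if weight is read in whole kilograms. A twofold step is in any case built into the banding, from 1.67 mg/kg at 12 kg to 3.08 at 13 kg. Both points are fair, and the gaps are therefore conditional. But rounding down and rounding to the nearest kilogram can lead to different rows, and no rule is stated.

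**The three-dose reading of AL is strained.** Daily need not mean once daily. Table B counts tablets by dose where the other charts count by day. The background calls AL dosing complex, section 3.12 singles AL out for direct observation, and the six-dose regimen is the one described with current packaging. So a reader might infer that the trial intends three AL doses, but the documents do not support that. They do not state any other count either. The figures in Appendices VI to VIII are not shown, and a dose count may stand there. Table B would still need to agree with it.

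**Confounding.** A reader might infer that uneven dosing confounds the efficacy comparison. It would not. Allocation is randomised within site (section 3.11), and section 3.6 analyses each site and pools with stratification by site. Each site's contrast stays a fair randomised comparison of the regimens given there. The risk is variation between sites in what those regimens were.

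**Conclusion.** The point holds in this limited form and should be settled before the chart is used.

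- **AL** is the most important part. No visible text fixes the number of doses for 1360 planned children, and the literal reading matches neither regimen in the background.
- **DHAPQ, 5-6 kg:** a plain internal contradiction. Both maxima are 25% above what the row delivers at 5 kg. It affects stated exposure only. The PPQ maximum for 24-35 kg is a small further miss.
- **DHAPQ between bands:** an ambiguity with a twofold consequence, conditional on weight being recorded more finely than 1 kg. How many children would fall in the gaps is unknown.

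The likely statistical effect is exposure that varies within an arm from site to site. That would be hard to separate from the site heterogeneity that section 3.6 sets out to investigate. It would be too broad to say that the trial's regimens are not fixed: CDA, AQ+AS and DHAPQ tablet counts at whole-kilogram weights are unaffected. The arithmetic does not show whether the band, the mg amount or the mg/kg figure in the 5-6 kg row is the wrong entry.

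**What to change.** The responsible clinicians and pharmacists should:

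1. reconcile the weight bands, mg amounts and mg/kg columns of Table A, including the PPQ maximum for 24-35 kg;
2. state how a weight between two DHAPQ bands is handled;
3. reconcile Table B with the treatment schedule and section 1.1 on the number and timing of AL doses, and check the Appendix VI to VIII figures against the result;
4. issue one corrected chart to all sites.

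This review does not say which dose, band or schedule is right. The cost is a corrected appendix page and a notice to sites; sample size and analysis do not change.
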